# Preliminary effect and feasibility of physiotherapy with strength training and protein-rich nutritional supplement in combination with anabolic steroids in cross-continuum rehabilitation of patients with hip fracture: protocol for a blinded randomized controlled pilot trial (HIP-SAP1 trial)

**DOI:** 10.1186/s13063-019-3845-y

**Published:** 2019-12-23

**Keywords:** Hip fracture, Rehabilitation, Physiotherapy, Strength training, Nutritional supplement, Protein, Anabolic steroid

## Abstract

**Background:**

A 2014 Cochrane review evaluating the effect of anabolic steroids after hip fracture concluded that the quality of the studies was insufficient to draw conclusions on the effects and recommended further high-quality trials in the field. Therefore, the aim of this pilot trial is to determine the preliminary effect and feasibility of a 12-week multimodal intervention consisting of physiotherapy (with strength training), protein-rich nutritional supplement and anabolic steroid on knee-extension muscle strength and function 14 weeks after hip fracture surgery.

**Methods:**

We plan to conduct a randomized, placebo-controlled pilot trial with 48 patients operated for acute hip fracture. The patients are randomized (1:1) to either (1) physiotherapy with protein-rich nutritional supplement plus anabolic steroid or (2) physiotherapy with protein-rich nutritional supplement plus placebo. Outcome assessments will be carried out blinded at baseline (3–10 days after surgery) and at 14 weeks after entering the trial. Primary outcome is the change from baseline to follow-up in maximal isometric knee-extension muscle strength in the fractured limb. Secondary outcomes are physical performance test, patient-reported outcomes, and measures of body composition.

**Discussion:**

If the trial is found feasible and the results show an indication of anabolic steroid being a relevant addition to further enhance the recovery of muscle strength and function in an enhanced recovery after surgery program, this trial will constitute the basis of a larger confirmatory trial.

**Trial registration:**

ClinicalTrials.gov, NCT03545347. Preregistered on 4 June 2018.

## Background

Sustaining a hip fracture is a common event with major consequences for the individual and society. Northern Europe has the highest incidence rates, led by Denmark, with age-standardized annual rates of 574 per 100,000 in women and 290 per 100,000 in men [1]. Furthermore, incidence rates are expected to increase worldwide due to the aging populations [2].

Patients sustaining a hip fracture experience an immediate loss of knee-extension muscle strength in the fractured limb [3–5]. Decreased lower limb muscle strength is associated with impaired function and disability [4, 6, 7], and it is an independent predictor of falls within 6 months of the hip fracture [8]. As such, a hip fracture often leads to loss of independence, change of residence, further fractures, and high mortality rates [9–13]. Thus, hip fractures pose a substantial economic burden to the health care system and society in general [2, 14, 15].

The evidence regarding rehabilitation following hip fracture shows positive effects on mobility after structured exercise interventions including progressive strength training [16–19]. However, these interventions are mainly started months after the hip fracture has occurred as prolonged programs following ceased standard rehabilitation [16–19]. This is costly and does not reflect the usual standard rehabilitation program offered to patients with hip fracture [20]. On the other hand, although a positive effect of structured exercise has been shown, it seems that these interventions alone are insufficient to overcome the major long-term negative impact of a hip fracture on physical function [10].

A recent (2014) Cochrane systematic review has evaluated the effect of anabolic steroids, either separately or in combination with nutritional supplements, in rehabilitation following hip fracture surgery in terms of functional outcome and adverse events (AEs) [21]. Although positive tendencies were identified in relation to activities of daily living and hip-related function [22, 23], quality of life [22], gait speed [23], and reduction in loss of muscle mass [22, 23], the quality of the studies was insufficient to draw definitive conclusions on the effect [21]. It was emphasized that further high-quality trials are warranted [21], and this is supported by several other narrative reviews in the field [6, 13, 24].

Another common and ongoing challenge to optimal recovery after hip fracture and hospitalization is low protein intake in elderly patients [25]. A recent Cochrane systematic review of the effect of nutritional supplementation for older patients recovering from hip fracture concluded that there might be some effect in relation to reducing complications within the first 12 months, but the evidence is weak [26].

On the basis of our previous early exercise studies [3, 27, 28] and review recommendations [6, 13, 16, 21, 25], it seems rational and strongly needed to apply an early multimodal intervention consisting of muscle-building medicine as well as nutritional and physical exercise treatment in order to enhance short- and long-term outcomes after the disabling event of a hip fracture.

### Purpose

The aim of this pilot trial is to investigate the preliminary effect and feasibility of a 12-week multimodal intervention consisting of physiotherapy (functional, balance, and strength training), protein-rich nutritional supplementation, and anabolic steroid (INT) compared with physiotherapy (functional, balance, and strength training), protein-rich nutritional supplement, and placebo (CON) in rehabilitation following hip fracture surgery on fractured limb knee-extension muscle strength at 14-week follow-up.

We hypothesize the following:
An intervention consisting of physiotherapy, nutritional supplementation, and anabolic steroid is a feasible and preliminary safe treatment in elderly patients with hip fracture when initiated in the acute orthopedic ward and continued for 12 weeks.This multimodal intervention (physiotherapy, nutritional supplementation, and anabolic steroid) is more efficacious in improving muscle strength and physical function 14 weeks after hip fracture surgery than physiotherapy, nutritional supplementation, and placebo.

## Methods

### Trial design

The HIP-SAP1 trial (Hip fracture, Strength training, Anabolic steroid and Protein) is a randomized, blinded, single-center, placebo-controlled, two-arm, parallel-group, superiority pilot trial. We intend to include 48 patients with hip fracture who will be randomized (1:1) to one of two arms.

This clinical trial protocol is based on the PREPARE trial guide [29], the SPIRIT (Standard Protocol Items: Recommendations for Interventional Trials) checklist (Additional file 1), and the CONSORT (Consolidated Standards of Reporting Trials) checklist (extension to randomized pilot and feasibility trials). The Template for Intervention Description and Replication (TIDieR) checklist [30] is used for description of the intervention. The trial was registered at ClinicalTrials.gov (identifier NCT03545347) before the first participant was included. The trial will be conducted at Copenhagen University Hospital Hvidovre in cooperation with all municipalities in the catchment area of the hospital.

### Recruitment

Patients admitted to the Hip Fracture Unit at the Orthopedic Department of Copenhagen University Hospital Hvidovre will be screened for eligibility (see inclusion and exclusion criteria in Table 1). The sampling method is consecutive, though screening and inclusion will be discontinued during trial staff’s absence. A screening log will be kept. Annually, approximately 475 patients above 60 years of age are operated at the Hip Fracture Unit. We assume that 20% would be excluded due to nursing home residency, another 20% would be excluded due to cognitive impairments, and the remaining criteria would account for approximately 25% exclusions. That would leave us with 14 eligible patients per month. We aimed at completion of recruitment within 1 year, but because recruitment has been lower than expected, the recruitment period has been extended to September 2020.

**Table 1 Tab1:** Inclusion/exclusion criteria

*Inclusion criteria*	
• Patients who have undergone surgery for a hip fracture at Amager-Hvidovre University Hospital and admitted to the Hip Fracture Unit at the hospital	
• Age ≥ 60 years	
• Ability to speak and understand Danish and having a Danish Social Security number	
• Able to give written informed consent	
• Residing at home and with an independent prefracture indoor walking ability (New Mobility Score ≥ 2)	
*Exclusion criteria*	
• Postoperative weight-bearing restrictions	
• Multiple fractures	
• Active cancer or suspected pathological fracture	
• Patient unable/unwilling to cooperate for testing and rehabilitation	
• Planned/elective hospitalization within the trial period	
• Cognitive dysfunction determined by chart review, reported by nursing staff, or observed by trained research staff (disoriented, dementia, active delirium)	
• Uncontrolled blood pressure (systolic > 150 mmHg or diastolic > 100 mmHg)	
• Heart disease in the form of peri-, myo-, or endocarditis	
• History of stroke with motor disability	
• Heart failure (New York Heart Association class III and IV)	
• Evidence of kidney failure or renal impairment (estimated glomerular filtration rate < 30 ml/min/1.73 m^2^ or serum creatinine > 200 μmol/L)	
• Abnormal liver function tests (alanine aminotransferase, γ-glutamyltransferase, bilirubin, or alkaline phosphatase > 2 times the upper limit of normal) or history of hepatic tumor	
• Elevated hematocrit ≥ 50%	
• History of breast or prostate cancer	
• Abnormally elevated serum prostate-specific antigen (PSA) assessed at the 3-week control* corresponding to PSA < 4.0 μg/L (60–70 years), PSA < 5.0 μg/L (> 70 years)	
• Allergic to any ingredient in the Deca-Durabolin solution (nandrolone, benzyl alcohol, arachis oil [peanut oil], and allergy to peanuts or soya) or milk protein allergy (related to the nutritional drink)	

*PSA during admission could be increased due to catheterization; therefore, PSA will be assessed at 3 weeks, and patients will be excluded at this time point if elevated values are identified

Information regarding inclusion and exclusion criteria will be obtained through medical records and by asking the patient or relatives. Assessment of eligibility is a two-stepped process because hematocrit and liver functions tests are not standard tests following hip fracture surgery, and therefore blood tests cannot be taken until after informed consent has been obtained.

The initial screening for eligibility will be conducted by the project coordinator, and final assessment of patients eligible for inclusion in the trial will be conducted by the principal investigator or two other medical doctors allocated to the hip fracture unit and trained in the protocol. These individuals will all be blinded to the allocation sequence.

Eligible patients will be addressed at the ward by the project coordinator 1–4 days following surgery. Patients will receive full oral and written information from the project coordinator about the purpose of the trial, process, and potential benefits and risks. The information is delivered by the project coordinator in simple language without technical or value-laden terms, and it is given in a considerate manner, tailored to the individual subject. The patients will be offered 24 h to consider participation, and they will be informed of the possibility of having a relative or other person accompanying them for further information. It is ensured that all questions the patient might have are answered. Patients who agree to participate must sign an informed consent form, which the project coordinator also signs for the given information.

Patients will be informed that participation is voluntary and that they can withdraw their consent at any time and leave the trial. It is emphasized that nonparticipation will not affect further treatment at the department.

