### Criteria for discontinuation

Safety parameters are listed under the “Secondary outcomes” heading and will be observed throughout the study. If values of hematocrit, liver tests, and prostate-specific antigen (PSA) exceed the safety thresholds, the treatment with Deca-Durabolin will be discontinued. Further, if women experience androgenic side effects, treatment will be discontinued. Regarding the remaining safety parameters, where no safety threshold is specified, values outside the reference interval will be evaluated by the medical doctors trained in the protocol and relevant action will be taken if necessary.

In accordance with the Declaration of Helsinki, patients have the right to withdraw from the trial at any time for any reason. Further, the investigator has the right to withdraw a patient from the trial at any time if a withdrawal is considered in the best interest of the patient.

Patients who have ceased intervention prior to its determination will be asked to follow the scheduled controls, and data will be collected according to the protocol. Patients who choose to withdraw from the trial will be asked the reason why. However, it is emphasized that the patient is not obliged to state the cause. If a patient drops out and is unwilling to follow the protocol, permission will be asked to continue weekly phone calls to monitor potential side effects (for 4 weeks after last injection). Further, the patient will follow standard treatment for hip fracture and see the orthopedic surgeon at the regular postoperative visit.

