#### Safety parameters

The following values are assessed: hemoglobin, hematocrit, creatinine, carbamide, sodium (Na^+^), potassium (K^+^), calcium, international normalized ratio (INR), liver tests, PSA, and glucose.

For the following parameters, safety thresholds are defined: hematocrit (safety threshold, values > 0.50), liver tests (albumin, alanine aminotransferase, γ-glutamyltransferase, bilirubin) (safety threshold, liver test values > 3 times the upper limit of normal), and PSA (safety threshold, increase to > 50%).

Other safety parameters are blood pressure (assessed using a digital blood pressure monitor, measured in mmHg) and facial hirsutism (assessed using the two face-related items of the modified Ferriman-Galwey hirsutism score, 0–8 points) [56], hoarseness (assessed through weekly interviews and hospital controls every 3 weeks), edema (assessed through weekly interviews and hospital controls every 3 weeks), and falls (a question regarding falls will be part of an interview guide used for the weekly telephone calls). Other AEs/adverse reactions (ARs) will be assessed through weekly interviews and hospital controls every 3 weeks.

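### Table 1 prints both week-3 PSA exclusion cut-offs with the inequality reversed; as a lesser point, albumin sits under a liver stopping limit it cannot reach in practice

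*Protocol article*

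**What the plan says.** **PSA.** The exclusion list in Table 1 (Methods, Recruitment) contains the row "Abnormally elevated serum prostate-specific antigen (PSA) assessed at the 3-week control* corresponding to PSA < 4.0" μg/L for ages 60–70, followed by < 5.0 μg/L for men over 70. The table footnote explains that catheterization can raise PSA during admission, and continues: "PSA will be assessed at 3 weeks, and patients will be excluded at this time point if elevated values are identified". Under Protocol amendment, a possibly false high value during admission is again the reason for moving the test to week 3.

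**Other upper limits in the same table.** Blood pressure is given as "systolic > 150 mmHg or diastolic > 100 mmHg", hematocrit as "Elevated hematocrit ≥ 50" percent, and the liver-test row ends "bilirubin, or alkaline phosphatase > 2 times the upper limit of normal) or history of hepatic tumor".

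**Liver stopping rule.** Safety parameters lists "liver tests (albumin, alanine aminotransferase, γ-glutamyltransferase, bilirubin) (safety threshold, liver test values > 3 times the upper limit of normal". Criteria for discontinuation says what follows if hematocrit, liver tests or PSA go too high: when they "exceed the safety thresholds, the treatment with Deca-Durabolin will be discontinued". For everything else it provides: "Regarding the remaining safety parameters, where no safety threshold is specified, values outside the reference interval will be evaluated by the medical doctors".

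**The concern.** The PSA row says one thing in words and the opposite in symbols. The words exclude high values; the symbols select low ones. The likely cause is that the normal range was printed where the exclusion limit belongs.

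This row is also the only absolute PSA limit in the document. The PSA threshold under Safety parameters is a relative one, based on a rise of more than 50%. A man whose PSA is high but stable is therefore caught only by Table 1. By week 3 he has had his baseline injection, and in the active arm he would go on to further doses of 100 or 200 mg.

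The albumin entry is a slip of a different kind. One upper-limit multiple is applied to every test in the liver list, and for albumin that multiple is out of reach. Because albumin then formally has a threshold, the medical review that Criteria for discontinuation reserves for parameters without one does not, as worded, extend to it.

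**Working it through.** The plan gives no calculated figure on this point, so there is none to reproduce. The check compares the texts and applies the printed rules to example values.

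**1. Direction of the PSA rule.** Three statements point upward: the opening words of the row, the footnote, and the amendment rationale. Two symbols point downward: < 4.0 and < 5.0.

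**2. Is this an artifact of reading the PDF?** The numeric limits in Table 1 that exclude for a value that is too high are:

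| Limit | Sign printed |
|---|---|
| Systolic pressure 150 mmHg | > |
| Diastolic pressure 100 mmHg | > |
| Serum creatinine 200 μmol/L | > |
| Liver tests, 2 × upper limit of normal | > |
| Hematocrit 50% | ≥ |
| PSA 4.0 μg/L (60–70 years) | < |
| PSA 5.0 μg/L (over 70 years) | < |

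Five of seven are signed correctly, and only the two PSA limits are not. The glomerular filtration limit (< 30) excludes for a low value and is also correct. Since >, ≥ and < all appear correctly elsewhere in the table, a conversion fault is unlikely.

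**3. The rule applied to example values (chosen for illustration).**

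| Age | PSA (μg/L) | As printed | Signs reversed |
|---|---|---|---|
| 65 | 3.0 | 3.0 < 4.0: excluded | kept |
| 65 | 8.0 | 8.0 is not < 4.0: kept | excluded |
| 75 | 4.5 | 4.5 < 5.0: excluded | kept |
| 75 | 8.0 | 8.0 is not < 5.0: kept | excluded |

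Every decision flips, and the reversed column is the one that agrees with the words.

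**4. The boundary.** If < 4.0 and < 5.0 are the normal range, the complement is ≥ 4.0 and ≥ 5.0, and a man of 65 with exactly 4.0 is excluded. If the intended sign was >, he is kept. The document does not settle which.

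**5. Albumin.** The document gives no albumin reference interval, so the upper limit is an assumption, taken over a range. Trigger = 3 × upper limit:

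- 3 × 40 = 120 g/L
- 3 × 45 = 135 g/L
- 3 × 50 = 150 g/L
- 3 × 55 = 165 g/L

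No value in that range can be reached in practice, so the albumin entry is inert whichever upper limit applies. The other three of the four listed tests (alanine aminotransferase, γ-glutamyltransferase, bilirubin) can exceed three times their upper limit and work as intended.

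**The case against.** The best defense of the PSA row is that it corrects itself. Heading, footnote and amendment rationale all give the direction, and doctors trained in the protocol make the final eligibility assessment. Staff would have to ignore the words to follow the symbols. This stands, and it is why the practical risk is low. It does not make the printed limit right.

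It is also fair that staff work from protocol version 7, which is not at hand, and that the misprint may exist only in the article. That stands too, and it decides the form of the correction.

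On albumin, the defense is that the list simply names a liver panel and then gives a panel threshold. The inert entry causes no wrong stop and hides no other trigger. Data monitoring expects that an out-of-range laboratory result may lead to clinical action, and the investigator may withdraw a patient at any time. This largely stands: the gap is one of wording, and no loss of oversight is shown.

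Three stronger readings are tempting and not supported:

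- A reader might infer that men with normal PSA were removed and men with high PSA kept. The document shows only what is printed, not how the rule was applied.
- A reader might infer that the liver stopping rule fails. Three of its four tests work.
- A reader might infer an error because alkaline phosphatase is an entry test but not a stopping test. The two lists need not match, the omission may be deliberate, and nothing in the document shows that it was meant in albumin's place.

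**Conclusion.** The PSA point holds on the document's own words and needs no outside figure: both age-specific cut-offs carry the wrong sign, against the criterion's wording and footnote. It is an error in an eligibility limit, but minor, because the intended direction is plain. It concerns men only, and the number of patients affected cannot be derived from the document.

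The albumin point holds as a secondary remark. It rests on an assumed upper limit of normal of 40–55 g/L, and the conclusion is the same across that range. Its consequence is small.

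Neither point bears on the sample size. Neither changes a rule of the efficacy analysis: Statistical analyses includes all randomized patients and treats safety parameters descriptively.

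Confidence is high for the printed article. Whether the working protocol has the same text is unknown.

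**What to change.** 1. **PSA, Table 1.** Reverse both inequalities so that elevated values exclude: ≥ 4.0 μg/L (60–70 years) and ≥ 5.0 μg/L (over 70 years) if the printed figures are the normal range, otherwise > 4.0 and > 5.0. The sponsor confirms which applies at the boundary.
2. **Albumin, Safety parameters.** Take albumin out of the rule on three times the upper limit and keep it as a measured safety parameter without a threshold. The doctors' review of values outside the reference interval then covers it as worded.
3. **Route.** The sponsor checks protocol version 7. If its text is correct, an erratum to the article is enough. If it has the same text, a short amendment is needed; this PSA criterion has been amended before.

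The cost is corrected wording in two places. Data collection, sample size and analysis stay as they are.

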#### Trial medication

Nandrolone is a synthetic anabolic-androgenic steroid; it is protein-building, promotes mineralization of bones, and stimulates the formation of red blood cells. Nandrolone is structurally related to naturally occurring testosterone, but it shows enhanced anabolic effect and a reduced androgenic effect. Nandrolone is used medically in the form of esters (nandrolone decanoate) and is intended for use in osteoporosis in postmenopausal women and for some types of anemia. Deca-Durabolin is an intramuscularly administered depot preparation of nandrolone decanoate.
*Active arm (INT)*: Patients will receive intramuscular injections of nandrolone decanoate (Deca-Durabolin 50 mg/ml; Aspen, Durban, South Africa) every 3 weeks. The first injection will be administered at baseline and the last injection at week 12. The solution is injected into the gluteal muscle or rectus femoris. The dosage varies, dependent on gender and testosterone level (men). Women will receive 50 mg, men with total testosterone ≥ 11 nmol/L will receive 100 mg, and men with total testosterone < 11 nmol/L will receive a dose of 200 mg. The cut of 11 nmol/L for total testosterone is determined on the basis of the age-related reference interval (men 50–70 years, 8.4–25.4 nmol/L) and lies below the mean value of 14.6 nmol/L (24).*Placebo arm (CON)*: Patients will receive a placebo injection of 1 ml of sodium chloride 9 mg/ml (produced by Fresenius Kabi, Bad Homburg, Germany), following the same intervals as for the active agent. The fluid is injected intramuscularly, and the product has no therapeutic effect.

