#### Protocol amendment

The following protocol amendments were approved by the ethics committee (28 September 2018) and the Danish Medicines Agency (26 October 2018):
The inclusion criterion *age* was changed from ≥ 65 years to ≥ 60 years. The cut ≥ 60 years is often used internationally when referring to elderly compared with nonelderly patients with hip fracture [59]. Further, patients from 60 to 64 years old would have the same potential benefit from the intervention.The exclusion criterion concerning *PSA* values was changed, so assessment of PSA is moved to the 3-week control, because a falsely elevated PSA value could be seen during admission due to urine catheterization.The exclusion criterion *terminal illness* was changed to *active cancer or suspected pathological fracture*.The time frame for baseline testing was changed from 6–10 days to 3–10 days due to short hospitalization for some patients.The intramuscular injection of trial medication was described to be administered in the gluteal muscle of the nonfractured leg. Due to difficulties with positioning all patients lying on the side, the description has been changed so that the medication can be administered either in the gluteal muscle or in the rectus femoris

A second protocol amendment concerning extension of the inclusion period until September 2020 has been approved by the ethics committee (27 September 2019) and the Danish Medicines Agency (22 July 2019). The primary investigator and the sponsor will inform the Research Ethics Committee, the Board of Health, and the Data Protection Agency if significant changes in protocol occur.

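### The PSA exclusion limits in Table 1 point the wrong way: elevated PSA is defined as a value below 4.0 or 5.0 μg/L

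*Protocol article*

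**What the plan says.** Table 1 of the protocol article (Methods, Recruitment) lists as an exclusion criterion "Abnormally elevated serum prostate-specific antigen (PSA) assessed at the 3-week control* corresponding to PSA < 4.0 μg/L (60–70 years), PSA < 5.0 μg/L", with the second figure attached to patients over 70.

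The footnote to the same table explains the timing. PSA measured during admission may be raised by catheterisation, so "PSA will be assessed at 3 weeks, and patients will be excluded at this time point if elevated values are identified". The Protocol amendment section gives the same reason: "assessment of PSA is moved to the 3-week control, because a falsely elevated PSA value could be seen during admission due to urine catheterization".

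Two other places bear on the point:

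- Under Safety parameters there is a separate on-treatment threshold, "PSA (safety threshold, increase to > 50" per cent. It is a relative rise with no absolute level. Under Criteria for discontinuation, exceeding it stops the study drug.
- Under Trial medication, injections are given every three weeks: "The first injection will be administered at baseline and the last injection at week 12".

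**The concern.** The words and the numbers of one criterion contradict each other. The words exclude men whose PSA is too high; the printed inequalities describe men whose PSA is below the limit. The likeliest explanation is that the age-specific normal ranges were printed where the exclusion limits belong.

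This matters because the limit is a safety decision rule for an androgenic drug. Men in the active arm receive 100 or 200 mg of nandrolone decanoate per injection, and a history of prostate cancer is itself an exclusion. The PSA decision is taken at week 3, when the patient has been randomised and has had one injection, so it determines whether exposure continues. Anyone who applied the numbers as printed, or copied the table into the larger confirmatory trial that this pilot is meant to inform, would have the rule backwards.

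**Working it through.** No stated figure needs reproducing. The check is one of logic and consistency.

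**1. The intended direction.** Three places agree. The criterion begins "Abnormally elevated serum prostate-specific antigen (PSA) assessed at the 3-week control". The footnote excludes on elevated values. The amendment moved the test because of falsely elevated values. All three aim at high PSA.

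**2. The printed direction.** The criterion continues "corresponding to PSA < 4.0 μg/L (60–70 years", and then gives < 5.0 μg/L for those over 70. Applying this rule to illustrative values (mine, not the article's):

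| Age | PSA (μg/L) | Printed test | Printed rule | Intended rule |
|---|---|---|---|---|
| 65 | 2.0 | 2.0 < 4.0, true | excluded | kept |
| 65 | 8.0 | 8.0 < 4.0, false | kept | excluded |
| 75 | 2.0 | 2.0 < 5.0, true | excluded | kept |
| 75 | 8.0 | 8.0 < 5.0, false | kept | excluded |

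The printed rule gives the wrong decision in all four cases.

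**3. Comparison with the rest of Table 1.** The other numeric exclusion limits are systolic pressure > 150 mmHg, diastolic pressure > 100 mmHg, estimated glomerular filtration rate < 30, serum creatinine > 200 μmol/L, liver tests > 2 times the upper limit of normal, and "Elevated hematocrit ≥ 50" per cent. Each marks the abnormal side: 6 of 6. For PSA it is 0 of 2.

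**4. Could it be a fault of text extraction?** Unlikely. The > sign in the over-70 age band on the same line is correct, and so are the >, < and ≥ signs elsewhere in the table.

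**5. Does anything else in the article supply the right limit?** No other section gives an absolute PSA value. The on-treatment threshold does not substitute for it: a man whose PSA is stable at 8.0 has a rise of (8.0 − 8.0)/8.0 = 0%, which is not above 50%, so treatment continues. Under Criteria for discontinuation, medical review of values outside the reference interval is provided for parameters without a specified threshold. PSA has one, so that provision does not expressly reach it.

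**6. How much treatment depends on the rule.** Injections every three weeks from week 0 to week 12 fall at weeks 0, 3, 6, 9 and 12, which makes 5. Blood sampling and injection take place at the same visit (General trial treatment procedures), and the article does not say whether the PSA result is available before the week-3 dose.

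- Result available first: 1 injection precedes the decision and 5 − 1 = 4 depend on it.
- Result available later: 2 precede it and 5 − 2 = 3 depend on it.

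The article gives neither the expected number of men nor a PSA distribution, so the number of patients affected cannot be calculated.

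**The case against.** The strongest reply is that the entry corrects itself. Its opening words and its footnote fix the direction, so the literal reading requires ignoring half of the criterion. The cut-off values and age bands are intact. Eligibility is decided by physicians trained in the protocol, a GCP unit monitors compliance, and the investigator may withdraw a patient in that patient's interest. Misapplication is therefore improbable. Moreover, this is a journal article, and the approved protocol, which is not shown, may carry the correct sign.

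Most of that stands, and it limits how serious the point is. There is no sign that any man was wrongly excluded or kept, and the error is demonstrated only for the published table. None of it makes the printed limit right. The article chose to state the limits and stated them in the wrong direction, so this is not a detail left to a fuller document.

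A further fair objection concerns the boundary. If the printed figures are the normal ranges, a value of exactly 4.0 or 5.0 is already outside normal, so changing < to > would leave that value unexcluded. The exact complement of the printed sign is ≥, which also matches the hematocrit criterion.

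**Conclusion.** The concern holds. Both PSA exclusion limits in Table 1 are reversed relative to the criterion's own wording, its footnote and the amendment rationale, and no other absolute PSA limit in the article offsets them. The rule governs 3 or 4 of the 5 planned injections, depending on when the week-3 result is available.

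The conclusion rests on the article's text alone. It assumes only that the words, which are consistent in three places, express the intent and that the signs are the slip. That the normal ranges were pasted in is a probable cause, not an established one. No effect on power, error rates or the analysis is claimed. The correction should be made because this is a safety limit, it is wrong as printed, and it costs almost nothing to put right.

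**What to change.** In Table 1, change the limits to exclusion at PSA ≥ 4.0 μg/L for ages 60–70 and ≥ 5.0 μg/L over 70. If the sponsor intends a value exactly at the limit to be acceptable, use > instead and say so.

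Then check two things: that the full protocol carries the same direction, and that the week-3 PSA decisions already taken followed it.

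The cost is two characters in the table, a clause for the boundary value if needed, and a short review of existing records. Sample size, randomisation and analysis are unchanged.
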